#### Randomization

Upon individual completion of the baseline survey by both partners, couples are randomized to either the home-based HIV testing arm or video-based CHTC with home-based HIV testing arm using a stratified 1:1 treatment allocation. The strata are based on two levels of serostatus: seroconcordant negative and serodiscordant. The treatment assignments are generated with the use of a pseudo-random number generator with permutated blocks that are used to ensure balance within stratum between the numbers of couples assigned to each treatment. The randomization process generates one of two emails to both study participants for the enrolled male couple, indicating whether they will be receiving home-based HIV testing or video-based CHTC with home-based HIV testing.

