### Statistical Analysis: Dyadic Characteristics

#### Overview

Dyadic characteristics will be analyzed within and between couples over time by HIV status and study arm (control vs experimental). Simple *t* tests and chi-square tests will be used to investigate systematic differences among average scales between experimental and control arms and between serodiscordant and seroconcordant-negative couples. Next, regression, generalized linear mixed models, and marginal models via generalized estimating equations (GEE) will be used to model longitudinal item and scale measures. In general, participants will be nested within couples, so the participant is regarded as the experimental unit; outcomes within couples and over time are potentially correlated. Initially, an unstructured serial correlation structure for the within-subject covariance and a single correlation parameter to describe the within-couple correlation will be assumed. If the unstructured covariance structure is too weak leading to nonconvergence issues and weak identification, more structure will be placed on the residuals and stronger models will be considered, such as an exchangeable or autoregressive correlation structure. Statistical inference will be likelihood based for the mixed models while generalized score and Wald tests will be used for statistical inference in the marginal models. In the presence of missing data, both mixed and marginal models accommodate missing data (eg, dropout), although the former under a weaker (missing at random) assumption.

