#### Sexual Risk-Taking

The definition of at-risk sex will be serostatus specific. For serodiscordant couples, at-risk sex will be CAI with either their main or outside partners. For seroconcordant-negative and seroconcordant-positive couples, at-risk sex will be CAI with outside sex partners. While data on PrEP use and adherence will be collected, the definition of at-risk sex focuses on condom use given the CDC recommendation for continued condom use for those adopting PrEP. The incidence of at-risk sex acts will be calculated as an incidence density, with the numerator being the number of individual at-risk sex acts and the denominator being person-years of follow-up time. Comparisons of the incidence of at-risk sex acts will be made by comparing incidence densities between the two arms. Incidence rates per couple-year of follow-up will be estimated and compared using exact methods based on the Poisson distribution by using the GEE approach. Baseline covariates include race, age, and duration of relationship. Period incidence rates—6-monthly incidence density rates—of at-risk sex will be estimated by performing a GEE Poisson regression analysis of the 6-monthly counts. This will be implemented using the PROC GENMOD procedure by SAS (SAS Institute Inc) [56] and using an exchangeable correlation structure for the repeated observations of couples. The incidence density ratio, or incidence rate ratio (IRR), is the ratio of the incidence density in one treatment group (intervention arm) to that of another group (control arm). Results by each baseline covariate will be summarized as the IRR and the 95% confidence interval. These analyses will be descriptive and include analyses stratified by race/ethnicity. Prevalence of each outcome will be calculated and prevalence of outcomes will be compared in the control and intervention groups using chi-square tests or Fisher’s exact tests, as appropriate.

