#### Linkage to Care

The percentage of HIV-positive respondents who receive a timely (<3 months) comprehensive visit—a visit including a CD4 count, viral load count, and the date of their first care visit—will be tested for significance across the two study arms. The percentages of couples who are seroconcordant negative, seroconcordant positive, and serodiscordant, as part of the description of the analysis samples, will be recorded. To assess whether the concordancy of the couple modifies the intervention effects, formal statistical tests—likelihood ratio tests in mixed models and generalized score tests in marginal models—of the null hypothesis will be conducted. The null hypothesis is that the two-way interaction effect for the aforementioned items and scales between intervention and concordancy is zero. If the statistical test does not reject the null hypothesis, the concordancy main effect in the model will be retained, removing the two-way interaction, and conclude that there is not sufficient evidence to suggest that concordancy modifies the intervention effect.

The safety of the intervention at both the individual and couple levels will be evaluated by examining reported IPV within the relationship and relationship dissolution. At the individual level, prevalence of each individual adverse outcome or any adverse outcome will be calculated. Prevalence of outcomes will be compared across the control and intervention arms, by serostatus of the couple, and by relationship duration using chi-square tests or Fisher’s exact tests, as appropriate. At the couple level, the APIM will be used to predict how an individual and his partner’s reports of dyadic characteristics affect the individual’s experience of IPV and reported relationship dissolution.

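### Couples are randomised, but the individual-level safety outcomes are compared between arms with chi-square or Fisher tests that ignore the pairing of partners

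*Protocol article*

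**What the plan says.** Under Randomization, the couple is the unit allocated: "couples are randomized to either the home-based HIV testing arm or video-based CHTC with home-based HIV testing arm using a stratified 1:1 treatment allocation", with serostatus as the stratum.

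The last paragraph under Linkage to Care deals with safety. The safety of the intervention "will be evaluated by examining reported IPV within the relationship and relationship dissolution". The level of the data is then given: "At the individual level, prevalence of each individual adverse outcome or any adverse outcome will be calculated". The next sentence gives the test: "Prevalence of outcomes will be compared across the control and intervention arms, by serostatus of the couple, and by relationship duration using chi-square tests". The alternative, where it suits the data, is Fisher's exact test. For the couple level the article turns to another method: "At the couple level, the APIM will be used to predict how an individual". That sentence goes on to name both partners' dyadic characteristics as predictors, and IPV and dissolution as outcomes.

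The Overview of the statistical analysis recognises the pairing: "participants will be nested within couples, so the participant is regarded as the experimental unit; outcomes within couples and over time are potentially correlated". It plans mixed models and GEE with a within-couple correlation parameter for longitudinal items and scales. Under Sexual Risk-Taking there is a similar chi-square sentence ("Prevalence of each outcome will be calculated and prevalence of outcomes will be compared in the control and intervention groups using chi-square tests"), but it does not say whether the records are men or couples.

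**The concern.** Two men in one relationship are not two independent observations of what the assigned arm does. Both receive the same allocation, and IPV and dissolution are events of the relationship. A chi-square or Fisher test on individual records counts each man as a separate unit of evidence and understates the variance of the arm difference. Dissolution is the extreme case: according to Process and Use of Communal Coping, each partner is asked about the status of the same relationship.

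These are the article's two stated safety measures. If the variance is too small, the trial may report a rise or fall in either outcome that is only chance, and an interval built on the same variance may seem to exclude a harm that it cannot exclude. The comparison by serostatus in the same sentence has the same problem, because serostatus type is shared by both partners.

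**Working it through.** **The plan's own figures.** The article gives no error rate for the safety tests. The nominal 5% appears only in the Sample Size example. The power figures there use couples as units. With two-sided 5% and proportions centred on 25%, they reproduce to within a point: 51.6%, 67.2% and 85.5% at 150 couples per arm (stated 52%, 67%, 85%), and 80.9%, 92.6% and 99.0% at 300 per arm (stated 81%, 92%, 99%). The power statement is therefore not touched by this point.

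**Inputs**
- Unit of randomisation: the couple, two men each (Randomization).
- Target: 400 couples, so 200 couples or 400 men per arm (Sample Size).
- Safety data: individual level, chi-square or Fisher (Linkage to Care).
- Within-couple ICC: not given. Assumed 0.3 to 0.5 for IPV. For dissolution it is near 1 if both partners' reports are entered, since they describe one event.

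**Formula.** For clusters of size m = 2 the design effect is 1 + (m − 1) × ICC = 1 + ICC. A test that assumes independence uses a standard error too small by √(1 + ICC), so its actual two-sided type I error is

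2 × [1 − Φ(1.96 / √(1 + ICC))].

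| ICC | 1.96 / √(1 + ICC) | Actual type I error |
|---|---|---|
| 0 | 1.960 | 5.0% |
| 0.3 | 1.719 | 8.6% |
| 0.5 | 1.600 | 11.0% |
| 0.8 | 1.461 | 14.4% |
| 1 | 1.386 | 16.6% |

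**Simulation check.** 200 couples per arm, no true arm effect, 20,000 trials per setting. Prevalence was 5%, 10% and 25% for chi-square, and 5% and 10% for Fisher.

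| ICC | Chi-square, uncorrected | Chi-square, continuity-corrected | Fisher |
|---|---|---|---|
| 0 | 4.8–5.2% | 3.4–4.3% | 3.3–4.0% |
| 0.3 | 8.2–8.8% | 6.2–7.4% | 6.4–6.8% |
| 0.5 | 10.4–11.3% | 8.0–9.8% | 8.6–9.2% |
| 1 | 15.8–17.1% | 13.9–14.5% | 14.2–14.7% |

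The formula describes the uncorrected chi-square test. Fisher and the continuity-corrected test start below 5% and so end lower, but at ICC 1 they still reach nearly three times the nominal level.

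**Effect on an interval.** Take 20% dissolution in each arm, the allowance in Sample Size, and 200 couples per arm.
- Men counted as independent: 1.96 × √(2 × 0.2 × 0.8 / 400) = 5.5 percentage points.
- Couples counted: 1.96 × √(2 × 0.2 × 0.8 / 200) = 7.8 percentage points.

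The ratio is √2 = 1.41.

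**The case against.** The strongest reply is that the article plans clustered methods and that the fault is narrow. Much of this stands.

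- A reader might infer that all individual outcomes, scales included, are tested at up to 17%. The text does not support that. The simple t and chi-square tests in the Overview are a first step, followed by mixed models and GEE with a within-couple correlation. Counts of at-risk sex acts are analysed by GEE Poisson regression.
- The chi-square sentence under Sexual Risk-Taking does not name individuals as the unit, and the section also works in couple-years. It is affected only where individual records are used.
- The article never says outright that dissolution enters as two records per couple. The Sample Size and Results sections count it by couple. The 14% to 17% therefore depends on taking the individual-level statement in the safety paragraph at its word.
- It might be argued that the Overview models, planned for items and scales, already cover IPV and dissolution. The article lists these two outcomes with the secondary dyadic measures but calls them additional to the framework. Coverage is not excluded, but the safety paragraph names its own tests, and these are the ones it assigns to the arm comparison.
- The phrase "the participant is regarded as the experimental unit" might be read as denying the clustering. The same sentence concedes it, so this is loose wording. Whether the APIM will carry an arm term is a detail that a full plan may settle. What can be said is only that, as described, the APIM is not an arm comparison.
- No stopping rule is tied to these tests, and the excess error is two-sided, so about half of it falls in the direction of false harm.

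None of this alters the safety paragraph itself, which names both the individual level and tests that assume independence.

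**Conclusion.** The concern holds for the safety comparison under Linkage to Care. As written, IPV, dissolution and any adverse outcome are compared between arms by tests that ignore the unit of randomisation, and the couple-level method described does not make up for it.

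For IPV the actual type I error is about 8.6% to 11% with an uncorrected chi-square test, and about 6.4% to 9.2% with Fisher. Both ranges rest on an assumed ICC of 0.3 to 0.5. For dissolution it is at most about 14% to 17%, depending on the test, provided that both partners' reports are counted and agree. The top of that range is a ceiling and not a figure for the trial's outcomes in general. The calculation ignores the serostatus strata. The sample size statement and the clustered models for scales and sex acts are unaffected.

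**What to change.** Reword the safety paragraph under Linkage to Care:

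- **Dissolution:** one record per couple, with a pre-stated rule for partners whose reports disagree. Compare arms with a serostatus-stratified test (Cochran-Mantel-Haenszel, or logistic regression with stratum).
- **Individual-level IPV and any adverse outcome:** logistic GEE clustered on couple with robust standard errors, including arm and serostatus stratum. The article already names GEE.
- **Prevalence tests under Sexual Risk-Taking:** the same approach wherever individual records are used.

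The preliminary t tests in the Overview need no change, because clustered models follow them.

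No new data are needed. The cost is wider standard errors: by a factor of √(1 + ICC), which is 1.14 at ICC 0.3, 1.22 at ICC 0.5 and 1.41 (41% wider) for a fully shared outcome. That is the precision the design actually has.

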#### Process and Use of Communal Coping

Several scales are also used to measure this element. The Outcome Efficacy to Reduce HIV Threat Scale discusses how communal coping involves couples working together and making decisions together to reduce the health threat. Three subscales were created to capture the full range of outcome efficacy related to these three processes of communal coping. For the first subscale, Joint Effort, the stem “My partner and I believe that ‘working together’ versus on our own is an effective strategy” is used. For the second subscale, Communication, the stem “Communicating with my partner is an effective strategy for...” is used. For the third subscale, Planning and Decision Making, the stem “My partner and I making decisions together rather than separately is an effective strategy” is used. The items for each of the three subscales were the same as the items used for the Preference for Sexual Health Outcomes Scale. The Couple Efficacy to Reduce HIV Threat Scale defines couple efficacy as a couple’s confidence that together they can engage in communal coping efforts.

In addition to the outcomes tied to Lewis’ framework [44], we also include two additional outcomes: violence and relationship dissolution. The Conflict Tactics Scale Revised [55] assesses both perpetration and experience of IPV. Relationship dissolution is assessed using an item that asks each partner in the couple to report the current status of their relationship and reason for dissolution at follow-ups.

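### Couples are randomised, but the only stated arm comparison for partner violence, relationship dissolution and any adverse outcome treats the two men of a couple as independent

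*Protocol article*

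**What the plan says.** The Randomization section of the protocol article allocates couples: "couples are randomized to either the home-based HIV testing arm or video-based CHTC with home-based HIV testing arm using a stratified 1:1 treatment allocation". Both men of a couple therefore always share an arm.

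The safety analysis is in the second paragraph of Linkage to Care, under Statistical Analysis. It first sets the unit: "At the individual level, prevalence of each individual adverse outcome or any adverse outcome will be calculated". The next sentence gives the test: "Prevalence of outcomes will be compared across the control and intervention arms, by serostatus of the couple, and by relationship duration using chi-square tests". Where suitable, Fisher's exact test takes its place. The paragraph then adds: "At the couple level, the APIM will be used to predict how an individual and his partner"; the sentence goes on to give the two partners' reports of dyadic characteristics as the predictors of IPV and dissolution. Study arm is not among them.

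On how dissolution is recorded, the section Process and Use of Communal Coping says: "Relationship dissolution is assessed using an item that asks each partner in the couple to report the current status of their relationship". The same section says that the IPV scale covers both committing and experiencing violence.

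Two other places bear on the unit. The Overview of the statistical analysis says that men are nested in couples, "so the participant is regarded as the experimental unit", and in the same sentence grants that outcomes within couples may be correlated. Sexual Risk-Taking says: "prevalence of outcomes will be compared in the control and intervention groups using chi-square tests", again with Fisher's exact test as the alternative, and does not say whether men or couples are counted.

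**The concern.** When couples are allocated, the information about the treatment contrast lies in the number of couples. A chi-square or Fisher's exact test on men assumes that every man is an independent observation. If partners' outcomes are positively correlated, the test understates the variance of the arm difference and rejects too often.

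Dissolution is the clearest case, because one break-up enters the table twice. IPV reports are also likely to be linked, since one man's perpetration is the other man's experience. A composite of any adverse outcome carries over part of the double counting of dissolution. The same applies to the comparisons by couple serostatus and by relationship duration, which are also characteristics of the couple.

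What is at stake is the safety conclusion. A chance imbalance in break-ups or violence could be declared a harm of video counselling, or a protection from it, well above the nominal 5% rate.

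**Working it through.** **1. The plan's own figures.** The document states no error rate or within-couple correlation for these tests. The nearest figures are the powers in Sample Size, which use couples as the unit. A two-sided 5% test of two proportions centred on 25% (25% minus d/2 against 25% plus d/2) gives:

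| Couples per arm, as stated | d = 10 | d = 12 | d = 15 | Stated |
|---|---|---|---|---|
| 150 | 51.6% | 67.2% | 85.5% | 52 / 67 / 85% |
| 300 | 80.9% | 92.6% | 99.0% | 81 / 92 / 99% |

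The figures reproduce with couples as the unit, so this point does not touch the sample size. They also support reading the 5% level as two-sided, which the text does not state.

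**2. Effect of counting men.** Let rho be the correlation between the two partners' outcomes. The sum of the two outcomes has variance 2p(1 - p)(1 + rho), whereas the test on men assumes 2p(1 - p). The design effect is 1 + rho, and the true error of a nominal 5% two-sided test is

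2 × [1 - Φ(1.96 / √(1 + rho))].

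| rho | 0 | 0.1 | 0.2 | 0.3 | 0.5 | 0.8 | 1.0 |
|---|---|---|---|---|---|---|---|
| True error | 5.0% | 6.2% | 7.4% | 8.6% | 11.0% | 14.4% | 16.6% |

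**3. Dissolution.** If both men answer and agree, every cell of the table is doubled and so is the chi-square statistic. The 5% critical value of 3.84 on men is then reached at 3.84 / 2 = 1.92 on couples. Its root is 1.96 / √2 = 1.386, with a two-sided tail of 16.6%.

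**4. Simulation.** No arm difference; 100 or 200 couples per arm; prevalence 5%, 10% or 20%; tests on men. The ranges are over those six settings.

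| rho | Chi-square | Fisher's exact |
|---|---|---|
| 0 | 4.4 to 4.9% | 2.6 to 3.9% |
| 0.2 | 7.1 to 7.9% | 5.0 to 6.4% |
| 0.5 | 10.2 to 11.2% | 7.0 to 9.8% |
| 1.0 | 16.6 to 17.2% | 13.1 to 14.8% |

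**5. Does another stated analysis supply a valid arm comparison?**
- The mixed and GEE models of the Overview are for longitudinal items and scales of the dyadic characteristics. IPV and dissolution are introduced separately, as two outcomes additional to that framework.
- The GEE Poisson model of Sexual Risk-Taking is for counts of at-risk sex acts.
- The couple-level model in the safety paragraph uses dyadic characteristics as predictors and does not name arm.

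For the safety outcomes, the test on men is the only arm comparison stated.

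**The case against.** The strongest reply is that the plan does take the dyad seriously. It grants within-couple correlation, puts a within-couple parameter in its models, evaluates safety at both individual and couple level, and applies a dyadic model to IPV and dissolution. All of that is so. It still leaves the safety comparison between arms without any adjustment for couples.

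A reader might infer four stronger things that the document does not support.

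- *That the scale comparisons are invalid too.* The simple t and chi-square tests are a first step, followed by models that carry a within-couple correlation. Only the preliminary P values are exposed.
- *That at-risk-sex prevalence is tested on men.* The section does not state the unit. It uses both person-years and couple-years for incidence, and its incidence comparison is already a GEE analysis with correlation for couples. The inflation arises only if men are counted.
- *That a range of about 7 to 17% is established.* It corresponds to rho from 0.2 to 1.0 with a chi-square test. No rho is given, smaller values give less, and Fisher's exact test is more conservative.
- *That published intervals will be too narrow by a known amount.* No interval is planned for these prevalence differences. Nor may 20% dissolution be applied to 200 couples per arm as the plan's own case, because Sample Size reaches 400 couples only after dissolution has been taken off.

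It is also fair that IPV and dissolution are not primary outcomes, and that too small a P value may err towards flagging harm. That lowers the stakes; it does not make the test valid.

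**Conclusion.** The point holds for the safety comparisons of IPV, relationship dissolution and any adverse outcome. The unit there is explicitly the man, the tests named assume independence, and no other arm comparison is stated.

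For dissolution, the true error of a nominal 5% test is about 16 to 17% with chi-square and about 13 to 15% with Fisher's exact test in the simulated settings. This rests on both partners responding and agreeing, so that rho is near 1; one-sided response or conflicting reports would reduce it. For IPV the size is conditional on an assumed rho: 6.2% at 0.1, 7.4% at 0.2 and 11.0% at 0.5 with chi-square, less with Fisher's. For any adverse outcome, rho is likewise not given.

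Elsewhere only clarification is needed: the Overview names the wrong experimental unit for a couple-randomised trial, and Sexual Risk-Taking leaves the unit of its prevalence tests open.

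**What to change.** 1. **Linkage to Care, safety paragraph.** Compare dissolution once per couple, with chi-square or Fisher's exact test on couples, and state how a couple is classified when the two reports differ or one is missing. Compare IPV and any adverse outcome with GEE clustered on couple and robust standard errors, or at couple level. A couple-level IPV outcome (for example, any report by either man) answers a different question from individual prevalence, so the choice should be stated. Treat the comparisons by serostatus and relationship duration in the same way.
2. **Overview.** Name the couple as the randomised unit. Label the simple t and chi-square tests as descriptive, with inference from the mixed or GEE models.
3. **Sexual Risk-Taking.** Run the prevalence tests on couples, or use couple-clustered GEE if men are counted.

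The cost is analysis wording and somewhat larger P values. No data collection, trial conduct or sample size changes.
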